## Abstract

**Background:**

Upper-extremity hemiplegia after stroke remains a significant clinical problem. The supplementary motor area (SMA) is vital to the motor recovery outcomes of chronic stroke patients. Therefore, rebuilding the descending motor tract from the SMA to the paralyzed limb is a potential approach to restoring arm motor function after stroke. Paired associative stimulation (PAS), which is based on Hebbian theory, is a potential method for reconstructing the connections in the impaired motor neural circuits. The study described in this protocol aims to assess the effects of cortico–peripheral Hebbian-type stimulation (HTS), involving PAS, for neural circuit reconstruction to rescue the paralyzed arm after stroke.

**Methods:**

The study is a 4-month double-blind randomized sham-controlled clinical trial. We will recruit 90 post-stroke individuals with mild to moderate upper limb paralysis. Based on a 1:1 ratio, the participants will be randomly assigned to the HTS and sham groups. Each participant will undergo 5-week HTS or sham stimulation. Assessments will be conducted at baseline, immediately after the 5-week treatment, and at a 3-month follow-up. The primary outcome will be the Wolf Motor Function Test (WMFT). The secondary outcomes will be Fugl-Meyer Assessment for Upper Extremity (FMA-UE), Functional Independence Measure (FIM), and functional near-infrared spectroscopy (fNIRS) parameters. The adverse events will be recorded throughout the study.

**Discussion:**

Upper-limb paralysis in stroke patients is due to neural circuit disruption, so the reconstruction of effective motor circuits is a promising treatment approach. Based on its anatomical structure and function, the SMA is thought to compensate for motor dysfunction after focal brain injury at the cortical level. Our well-designed randomized controlled trial will allow us to analyze the clinical efficacy of this novel Hebbian theory-based neuromodulation strategy regarding promoting the connection between the cortex and peripheral limb. The results may have significance for the development and implementation of effective neurorehabilitation treatments.

**Clinical Trial Registration:**

[www.ClinicalTrials.gov], identifier [ChiCTR2000039949].

## Background

The 2013 National Epidemiological Survey of Stroke (NESS) in China reported a large and increasing burden caused by stroke, with approximately 11 million prevalent cases of stroke, 2.4 million new-onset cases of stroke, and 1.1 million stroke-related deaths in China annually, which match the long-term trends (Wu et al., 2019). Upper-extremity hemiplegia after stroke remains a clinical challenge, with only 20% of patients currently recovering normal hand function (Kwakkel et al., 2003). Common rehabilitation options to improve arm motor function include physical fitness therapy, task-oriented practice, constraint-induced movement therapy, and robot-assisted therapy. However, the clinical outcomes tend to be modest, and several disabilities remain unresolved and need further research.

In the search for improved stroke treatments, scientists have been trying to identify the link between motor function recovery after stroke and cortical reorganization, mostly focusing on plastic changes in the sensory cortex (S1), primary motor cortex (M1), supplementary motor area (SMA), premotor cortex (PMC), and cerebellum (Qing and Li, 2015). The PMC and SMA, which contribute fibers to the corticospinal tract, are major cortical regions of voluntary action plan formation and initiation (Calautti et al., 2007). They are believed to play a role in the temporal control of movement and are critical in motor function recovery in stroke patients (Kantak et al., 2012). The SMA has been reported to be a key brain area for motor function recovery after left subcortical stroke (Wan-Wa et al., 2013). As a part of the internal capsule, about 10% of the corticospinal tract fibers arise from the SMA and terminate in the spinal cord (Baran et al., 2016). The motor neurons innervating the hand muscles are mostly located at the lower cervical segments (C7–T1). A retrograde tracer study by Dum and Strick (2002) showed that corticospinal efferents from the SMA in macaques largely project to these segments. In chronic stroke patients, the overlap index of the SMA is positively associated with the Motor Status Scale (MSS) forearm-specific score (Wan-Wa et al., 2013). Schulz et al. (2017) found that the residual motor function output of chronic stroke patients depends on the degree of disruption to the corticospinal tract and fibers connecting M1 and the ventral premotor cortex. Anne et al. (2011) reported that the positive coupling of the SMA and PMC with the ipsilesional M1 decreased during the acute phase of stroke. The coupling parameters between these regions increased with increased motor recovery, which can be used to predict improved outcomes (Anne et al., 2011). Therefore, rebuilding the descending motor tract from the SMA to the peripheral limb is a potential approach for arm motor function restoration after stroke.

Recently, it has become popular to use non-invasive neuromodulation combined with standard upper-limb rehabilitation for functional restoration in patients with post-stroke hemiplegia (Edwardson et al., 2013). Repetitive transcranial magnetic stimulation (rTMS) is a non-invasive treatment that rarely induces pain caused by skin impedance and has the advantage of non-invasively stimulating deep tissue areas. However, studies on the effects of TMS in stroke have mostly focused on the activation of single targets to promote focal neuron function recovery. In the 2014–2018 evidence-based guidelines on the therapeutic use of rTMS by International Federation of Clinical Neurophysiology (IFCN), several sham-controlled studies of ipsilesional high-frequency rTMS or intermittent theta-burst stimulation (iTBS) in post-stroke patients led to improvements (from marginal to significant) in balance or paretic hand motor function (Lefaucheur et al., 2020). Unfortunately, a key study on hand motor recovery during the chronic stroke stage found that 1-Hz rTMS over the contralesional M1 was not superior to sham rTMS (Harvey et al., 2018).

Our objective is to effectively restore neural circuits after stroke. Neural circuit reconstruction is similar to sensorimotor learning based on the Hebbian principles of neural plasticity. Donald Hebb Huibert et al. (2019) hypothesized that, if the activity in a presynaptic neuron is repeatedly temporally correlated with postsynaptic neuron activation, a long-lasting alteration in synaptic structure will ensue. It is highly likely that activation of a presynaptic neuron excites the postsynaptic neuron (“neurons that fire together wire together”). The Hebbian theory is widely utilized in artificial neural networks. We think that neural circuit reconstruction will be possible based on Hebbian synaptic plasticity.

Paired associative stimulation (PAS), based on Hebbian theory with a specific time interval, is an important means by which to reconstruct neural circuits. Traditionally, PAS was performed by delivering a peripheral afferent volley using electronic stimulation over the radial or median nerve prior to TMS over M1. Peripheral magnetic stimulation (PMS) can also be applied, for example to the muscles, spinal nerve roots, and peripheral nerve fibers. PMS can directly recruit 1A afferent fibers or indirectly provide strong proprioceptive inflow related to muscle contraction or the change in a joint angle, while peripheral electronic stimulation generates a significant cutaneous inflow in the afferent fibers of the lemniscus and spino-thalamic tract. Unlike peripheral electronic stimulation, PMS is painless and well tolerated (Beaulieu and Schneider, 2015). A study of 16 healthy participants revealed that PMS could modulate cortical excitability (Sato et al., 2016). Krewer et al. (2014) investigated the effect of repetitive PMS on upper-limb muscular spasm caused by stroke or brain trauma. They reported short-term effects on spasticity for wrist flexors and long-term effects on spasticity for elbow extensors (Krewer et al., 2014). Another group investigated the effect of integrated PMS and TMS in healthy participants. They found that PAS can upregulate corticospinal excitability and downregulate intracortical inhibition (Sato et al., 2016).

We aim to use PAS to rebuild a neural circuit involving SMA → internal capsule → periphery in order to restore motor function. We will perform timely coupled stimulation of presynaptic and postsynaptic neurons to restore the motor circuits instead of simply upregulating excitation in the lesion area. If HTS can be induced non-invasively by magnetically stimulating the peripheral nerve after magnetically stimulating the SMA in the human brain, this method may provide a neuromodulation approach to rebuild the motor network after stroke. We hypothesize that PMS of the peripheral nerve tens of milliseconds after TMS of the SMA related to the functioning of the upper extremities will induce spike timing-dependent plasticity. This will increase targeted cortical excitability and help to reconstruct sensorimotor pathway conduction to facilitate arm motor function recovery.

## Objectives

The main objectives of this clinical trial are to (1) investigate whether HTS can promote arm motor function recovery in chronic stroke and (2) explore the underlying mechanisms in the brain after HTS using functional near-infrared spectroscopy (fNIRS).

## Trial Design

This protocol has been designed according to the Standard Protocol Items: Recommendations for Interventional Trials (SPIRIT) guidelines. It is registered with the Chinese Clinical Trial Registry. Based on a 1:1 ratio, 90 participants will be randomly assigned to the HTS and sham groups. The prospective, single-center, double-blind, randomized, sham-controlled clinical trial will study the therapeutic effects of HTS vs. sham intervention. Each patient will undergo 1 session of real/sham HTS per day, always followed by general rehabilitation therapy, 5 days per week, with a total of 25 sessions. Three assessments will be performed in both groups: at baseline, immediately after the 5-week treatment, and at a 3-month follow-up. The effects will be measured using a variety of rating scales. The primary outcome will be the Wolf Motor Function Test (WMFT). The secondary outcomes will be the Fugl-Meyer Assessment for Upper Extremity (FMA-UE), Functional Independence Measure (FIM), and fNIRS parameters. To strengthen treatment compliance and minimize dropout, a doctor will contact the participants regularly.

## Recruitment and Sample Selection

Participants will be recruited from Shanghai Yangzhi Rehabilitation Hospital affiliated with Tongji University. Recruitment began on 11 Nov 2020 and will continue until the required sample size has been achieved. The volunteers will be carefully screened based on the inclusion and exclusion criteria. All participants, who will be given verbal and written details on the study purpose and process, will sign a written informed consent form.

## Stroke Diagnosis

Stroke will be diagnosed based on the World Health Organization definition in 1970, “stroke is rapidly developing clinical signs of focal (or global) disturbance of cerebral function, with symptoms lasting 24 h or longer, or leading to death, with no apparent cause other than of vascular origin” (Graeme, 2017).

## Eligibility Criteria

The inclusion criteria are as follows:

(1) Having a first unilateral supratentorial, ischemic stroke, and having had a stroke in 4–12 month;

(2) Upper extremity dysfunction, with FMA-UE motor score of 30–60 out of 66 (Fugl-Meyer et al., 1975);

(3) Aged 18–80 years, regardless of sex;

(4) Mini Mental State Examination (MMSE) score > 24;

(5) Written informed consent;

(6) Right handedness.

The exclusion criteria (based on the TMS safety criteria proposed by Wassermann, 1998) are as follows:

(1) Metal implant device in the head, neck, or stimulation area;

(2) Medical implant device (cardiac pacemaker or cochlea implant);

(3) Pregnancy;

(4) Current or history of epilepsy;

(5) Current or history of medications known to affect central nervous system excitability;

(6) Intracranial hypertension;

(7) Unstable fractures or joint contracture.

(8) Taking drugs that may increase the risk of epilepsy or reduce cortical excitability.

## Randomization

The participants will be randomly assigned (using computer-generated random numbers) to one of the two groups in a 1:1 ratio after baseline assessment. A research assistant (who will not be involved in eligibility screening, the intervention, outcome assessment, or data analysis) will independently conduct the randomization process following allocation concealment. The allocation sequence will be concealed from the therapists, outcome assessors, data analysts, participants, and participants’ relatives.

## Sample Size Estimation

The calculation of the sample size was based on data from previous research and our per experiment (Lai et al., 2015). As the study involves two groups, the following sample size calculation for a two-sample mean comparison was used:

$$n_{c}=\frac{{\left(Z_{1-\alpha }+Z_{1-\beta }\right)}^{2}\,\sigma^{2}\,\left(1+\frac{1}{K}\right)}{{\left(\mu_{T}-\mu_{C}-△\right)}^{2}}$$

where, Z_1–_*_α_* = 1.960, Z_1–_*_β_* = 0.842, μ_*T*_=6.6 (predicted mean in HTS group); μ_*C*_=2.3 (predicted mean in sham group), σ = 2.0 (standard deviation), *K* = 1 (ratio of participants in the HTS and sham groups), Δ = 3 (optimality bounds), α = 0.025 (2.5% one-tailed significance level), and β = 0.20 (80% power). The calculated required sample size was 37 participants per group. Assuming a 20% dropout rate, 45 participants per group (a total of 90 participants) need to be recruited.

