### Statistical Analysis

Statistical analysis will be performed using SPSS 22.0 (SPSS Inc., Chicago, IL, United States). Database management and statistical analysis will be performed by an independent researcher, who will be blinded to group allocation. Monitoring of AEs will be carried out by the treating physical therapists. The primary analysis, which will be a per-protocol analysis, will include the patients who underwent the treatment course and completed the 3-month follow-up.

Descriptive statistics will be used to describe the baseline characteristics of the participants in both groups. The normally distributed continuous data will be presented as mean ± standard deviation, and the non-normally distributed continuous data will be presented as median (maximum and minimum). The Shapiro–Wilk test will be used to evaluate data normality. Homogeneity of variance will be assessed by Levene’s test. For the normally distributed continuous data (including WMFT, UE-FMA, and FIM), paired *t*-tests will be used to compare between baseline and postintervention in each group. Additionally, unpaired *t*-tests will be used to assess the differences in the baseline characteristics and the primary and secondary outcomes between the HTS and sham groups. For the non-normally distributed continuous data, Wilcoxon tests will be used. The one-tailed significance level (α) for statistical hypothesis testing will be set at *P* < 0.025 (Figure 2).

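### The sample size is calculated for superiority by a margin of 3, but the described t-test carries no margin, so the stated 80% power does not belong to it

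*Protocol article*

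**What the plan says.** Under Sample Size Estimation, the protocol article uses a two-sample formula for means whose denominator is the squared expected difference after a margin has been subtracted. The inputs are "6.6 (predicted mean in HTS group"), "2.3 (predicted mean in sham group"), "σ = 2.0 (standard deviation"), "Δ = 3 (optimality bounds"), "α = 0.025 (2.5% one-tailed significance level") and "β = 0.20 (80% power"), with equal allocation. The result is 37 per group, raised to 45 per group (90 in total) for 20% dropout. The section does not name the outcome or time point to which the means, SD and margin belong, or say whether the means are changes or final scores.

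Under Statistical Analysis, unpaired t-tests "will be used to assess the differences in the baseline characteristics and the primary and secondary outcomes between the HTS and sham groups". Wilcoxon tests replace them for non-normal data, and the level is one-tailed 0.025. No margin, shifted null or confidence-limit rule is given. The primary analysis set is the per-protocol completers.

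The Objectives section asks whether the Hebbian-type stimulation (HTS) promotes recovery of arm function. It names no minimum difference. The margin appears only under Sample Size Estimation.

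**The concern.** A margin in the denominator makes this a superiority-by-margin calculation with H0: difference ≤ 3. The power obtained is the probability of rejecting that null. An unpaired t-test with no margin tests, by default, whether the difference is zero. On that reading the power statement and the described test answer different questions.

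What is at stake is the meaning of a positive result. If the observed difference fell between about 1 and about 4, one reading of the plan would call the trial positive and the other would not. With nothing in the article to settle it, the choice could be made after the data are seen.

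**Working it through.** **Inputs.** From Sample Size Estimation: means 6.6 and 2.3 (difference 4.3), SD 2.0, margin 3, z-values 1.960 and 0.842, K = 1, 45 recruited per group, 20% dropout. Evaluable per group: 45 × 0.8 = 36. Assumption: the units are WMFT score points, WMFT being the primary outcome.

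**1. The plan's own figure.**
(1.960 + 0.842)² × 2.0² × 2 / (6.6 − 2.3 − 3)² = 62.81 / 1.69 = 37.17. The stated 37 reproduces, rounded down.

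**2. The same inputs without the margin.**
62.81 / 4.3² = 62.81 / 18.49 = 3.40, so 4 per group by the formula. With the t distribution, 4 per group gives 72% power and 5 give 84%, so 5 are needed. The stated 37 depends on the margin.

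**3. Smallest observed difference that is significant, 36 per group.**
SE = 2.0 × √(2/36) = 0.471; t(0.975, 70) = 1.994.
- Zero null: 1.994 × 0.471 = 0.94.
- Margin null: 3 + 0.94 = 3.94.

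The gap between the two thresholds is always the margin. Their level depends on n and SD:

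| n per group | SD | Zero null | Margin null |
|---|---|---|---|
| 36 | 2.0 | 0.94 | 3.94 |
| 37 | 2.0 | 0.93 | 3.93 |
| 45 | 2.0 | 0.84 | 3.84 |
| 36 | 3.0 (assumed) | 1.41 | 4.41 |

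**4. Probability of a significant result, 36 per group, SD 2.0 (noncentral t).**

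| True difference | Zero null | Margin null |
|---|---|---|
| 1.5 | 88% | below 0.01% |
| 3.0 | above 99.9% | 2.5% |
| 4.3 | above 99.9% | 78% |

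At a true difference of 4.3 the margin test has noncentrality 1.3 / 0.471 = 2.76. Its power is 77.6% at 36 per group and 78.8% at 37.

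**5. Difference detectable with 80% power under a zero null, 36 per group.**
2.802 × 0.471 = 1.32, or about 1.3 points. At an assumed SD of 3 it is 2.802 × 3 × √(2/36) = 1.98.

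**The case against.** The strongest reply is that the zero null is inferred. The article writes out no hypotheses and no success rule, an unpaired t-test can be run against a shifted null, and both sections use the same one-tailed 0.025. Formal hypotheses may stand in a full protocol or analysis plan that is not shown. This is right as far as it goes: one cannot say that the trial will certainly run a zero-null test. But the article does fix the test, the level and the sidedness, and it omits the one quantity on which its sample size depends. The sentence that covers the primary outcome also covers baseline characteristics and secondary outcomes, where one common shift of 3 would make no sense. Zero is therefore the natural reading.

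A second reply is that a zero-null test does no harm: its one-sided type I error stays at 2.5%, and on the plan's inputs it has more power than stated. That stands. A reader might infer that the trial is underpowered or that false positives against no effect are inflated; the figures show neither.

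A reader might also infer that the plan has defined success as a difference above 3 and that the analysis breaks this rule. The documents do not support that. The margin is only a sizing input, and the objective fits a zero null.

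**Conclusion.** The point holds as an inconsistency between two sections of the article. The 37 per group and 80% power belong to a test of H0: difference ≤ 3, and the analysis described has no margin. On the plan's SD and 36 evaluable per group, the two readings put the threshold for significance at 0.94 or 3.94. Power at 4.3 is above 99.9% or about 78%; neither is the stated 80%.

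The mismatch does not depend on the SD, but the thresholds do. It is tempting to say that success could be declared on less than one-third of the margin. At SD 2.0 that is so (0.94 / 3 = 31%). At 36 per group, however, the zero-null threshold reaches 1.0 at an SD of 1.0 / (1.994 × √(2/36)) = 2.13, and at 37 per group at about 2.16. The fraction is therefore not a firm feature of the design.

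The conclusion rests on two assumptions: that an unpaired t-test with no stated margin tests zero, and, for the word points, that the sizing inputs are WMFT scores.

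**What to change.** Use one null hypothesis in both sections, decided and recorded before unblinding. In either case, name the outcome, the time point and whether the means are changes or final scores.

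(a) Delete the margin. This fits the stated objective. Replace the justification with: 36 evaluable per group detect a difference of about 1.3 points with 80% power, one-sided 0.025, SD 2.0. The cost is that the trial can no longer claim, from its primary test, a benefit exceeding 3.

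(b) Keep the margin. State H0: difference ≤ 3 in the analysis section and declare success only if the lower limit of the two-sided 95% confidence interval exceeds 3. Give a matching shifted test for the Wilcoxon branch, for example by subtracting 3 from each HTS value before ranking. Restate power as about 78% at 36 evaluable per group. The cost is that success is harder to declare, with power slightly below the 80% planned.

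Either option takes a few sentences. Neither by itself requires more patients, unless under (b) the sponsor wants the full 80%.

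### With 45 recruited per group and the stated 20% dropout, 36 remain: fewer than the plan's own 37, and about 1 to 2 points short of 80% power on the margin-of-3 basis

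*Protocol article*

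**What the plan says.** The Sample Size Estimation section of the protocol article prints a formula for comparing two means with a margin, and all of its inputs: "6.6 (predicted mean in HTS group"), "2.3 (predicted mean in sham group"), "σ = 2.0 (standard deviation"), a margin Δ of "3 (optimality bounds"), equal allocation (K = 1), "α = 0.025 (2.5% one-tailed significance level") and "β = 0.20 (80% power"). The normal quantiles are given as 1.960 and 0.842.

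Its result is: "The calculated required sample size was 37 participants per group". The next sentence reads: "Assuming a 20% dropout rate, 45 participants per group (a total of 90 participants) need to be recruited". No formula is printed for the step from 37 to 45.

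The Statistical Analysis section makes the primary analysis per-protocol, in patients who had the treatment course and completed the 3-month follow-up. It compares the groups by unpaired t-tests (Wilcoxon tests if the data are not normal) and mentions no margin.

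**The concern.** The two sentences on numbers do not agree. One fixes how many participants per group are needed. The next fixes how many to recruit so that the need is still met after 20% dropout. Losing 20% of 45 leaves 36, so the recruitment figure misses the requirement that it is meant to protect. This can be seen from the two sentences alone, however the 45 was obtained.

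The dropout allowance matters here because the primary analysis is restricted to completers. A patient who drops out contributes nothing to it, so the allowance acts directly on the analysed number. At stake is whether 80% power at 20% dropout, as the section implies, is a property of the design.

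**Working it through.** **Inputs** (all from Sample Size Estimation): means 6.6 and 2.3, margin 3, SD 2.0, K = 1, quantiles 1.960 (one-sided 0.025) and 0.842 (80% power), dropout 20%, 45 recruited per group.

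**1. The plan's own figure.** The effective difference is 6.6 − 2.3 − 3 = 1.3.

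n = (1.960 + 0.842)² × 2.0² × (1 + 1/1) / 1.3² = 7.851 × 4 × 2 / 1.69 = 37.17 per group.

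The stated 37 is this value rounded down. A minimum sample size is rounded up, which gives 38.

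**2. The dropout step.**

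- Multiplying by 1.2: 37 × 1.2 = 44.4, which rounds up to 45 and matches the protocol.
- Dividing by 0.8: 37 / 0.8 = 46.25, so 47 per group (94 in total).
- Dividing by 0.8 from 38: 38 / 0.8 = 47.5, so 48 per group (96 in total).
- What 45 delivers: 45 × 0.8 = 36.

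**3. How much loss 45 per group can absorb.** To keep 37, at most 8 of 45 may be lost (17.8%). To keep 38, at most 7 of 45 (15.6%).

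**4. Power against the margin of 3.** By the normal formula, power = Φ(1.3 / (2.0 × √(2/n)) − 1.960). For n = 36 the standard error is 2.0 × √(2/36) = 0.471, the ratio is 2.758, and Φ(0.798) = 78.7%. The t column uses the noncentral t distribution with 2n − 2 degrees of freedom at one-sided 0.025.

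| Evaluable per group | Normal formula | t-test |
|---|---|---|
| 36 | 78.7% | 77.6% |
| 37 | 79.8% | 78.8% |
| 38 | 80.9% | 79.9% |
| 39 | – | 80.9% |

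**5. Where the shortfall comes from.** By the protocol's formula, rounding 37.17 down to 37 costs 80.0 − 79.8 = 0.2 points. Falling from 37 to 36 costs a further 79.8 − 78.7 = 1.1 points. The total is 1.3 points. With the t-test the total is 80.0 − 77.6 = 2.4 points; the additional 1.1 points reflect the change of method.

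**6. The same 36 per group without a margin.** If the test is a plain comparison of means, as the Statistical Analysis section describes, the ratio is 4.3 / 0.471 = 9.1. Power is then essentially 100%, and about 4 per group would be enough for 80% by the same formula.

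**The case against.** Four points can fairly be made on the other side.

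- **The effect is slight.** By the protocol's own method the gap is 1.3 points. An SD of 2.0 × √(36 / 37.17) = 1.97 instead of 2.0 would remove it, and the inputs are given to only one decimal. This stands, and it limits the finding to a correction of the statement. It does not make the two sentences agree.
- **Rounding 37.17 to 37 is harmless.** At 37 the normal formula gives 79.8%, which is 80% as usually reported. This stands too: rounding up is the better convention, but the rounding alone would not be worth raising.
- **The multiplication by 1.2 is inferred.** The protocol prints no inflation formula. The inference fits the figures and division by 0.8 does not, but only the outcome, 36 remaining, can be verified. The finding needs only that outcome.
- **The planned test names no margin.** For a plain unpaired t-test on a 4.3-point difference with SD 2.0, 36 per group is far more than enough. This stands as a limit on the consequence: the loss of power exists only for a test against the margin of 3. It does not rescue the calculation, which the protocol bases on that margin.

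A reader might infer from the recruitment error that the trial is seriously underpowered, or that the primary analysis as described cannot reach 80% power. The documents support neither reading. The gap is 1 to 2 points on the margin basis, and there is none for the margin-free test at the predicted difference.

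**Conclusion.** The point holds as a small arithmetic error in the stated justification. On the protocol's own figures, 45 per group with 20% dropout leaves 36, against 37 stated and 38 when the formula is rounded up. Relative to a recruitment target that would keep those numbers, the total of 90 is 4 or 6 patients short. Power at 20% dropout is 78.7% by the stated formula, or 77.6% with a t-test, instead of 80%.

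This rests on the printed means, SD and margin, on 20% loss in each group, and on dropouts being excluded from the primary analysis, as the Statistical Analysis section provides. It applies to the hypothesis tested against the margin of 3. That the sample size uses a margin which the planned between-group test does not mention is a separate and larger mismatch; correcting the dropout arithmetic does not settle it.

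**What to change.** Keep the total of 90 and correct the Sample Size Estimation text to say that:

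- the stated normal formula requires 38 evaluable participants per group;
- 45 recruited per group leaves 36 at 20% dropout, with about 79% power by that formula (about 78% with a t-test);
- 80% power by that formula holds up to about 15% dropout (38 of 45 retained);
- these figures refer to the test against the margin of 3.

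The method behind each power figure should be named, because 38 per group reaches 80% by the normal formula (80.9%) but falls just under it with a t-test (79.9%; 39 per group gives 80.9%).

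The cost is a few corrected sentences and a slightly less favourable power statement, with no extra patients and no change to the analysis. If the sponsor prefers to keep the claim of 80% power at 20% dropout by the stated formula, recruitment would have to rise to 48 per group, 96 in total. Whether the primary test uses the margin should be reconciled between the two sections as its own item.
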